## Abstract

**Background:**

There is only limited information about the health effects of regular vaping. Research on the health status of people who used to smoke faces the challenge that previous smoking may have caused unknown health effects. Only studies of people who vape but have never smoked combustible cigarettes can enable the detection of harms attributable to vaping. Large prospective studies of well-characterized electronic cigarette users with and without a history of combustible cigarette smoking are warranted to establish the long-term effects of regular vaping on respiratory health.

**Objective:**

We will conduct a global cross-sectional survey of individuals from 6 world regions. Respiratory symptoms will be assessed using a validated questionnaire—the Respiratory Symptom Experience Scale (RSES). Current vapers who are nonusers of other tobacco or nicotine products will be compared with matched controls who are nonusers of vapes and other tobacco or nicotine products.

**Methods:**

This will be a multicountry, cross-sectional internet-based survey of 750 adults aged ≥18 years who satisfy the criteria for inclusion in either a cohort of people who exclusively vape and who are nonusers of other tobacco or nicotine products (“vapers cohort”; target N=500) or a cohort of nonvapers who are also nonusers of other tobacco or nicotine products (“controls cohort”; target N=250). The primary end point of the study is the RSES score. RSES scores of people in the “vapers cohort” will be compared with those of people in the “controls cohort.” Additionally, the study will collect data to characterize patterns of vaping product use among the vapers cohort. Data collection will include information about the age initiation of using vape products, reasons for starting and continuing the use of vape products, specific types of products used, flavors and nicotine strengths of recently used products, as well as the frequency and intensity of product use in the past 30 days.

**Results:**

Participant recruitment started in April 2023, and enrollment was completed by November 2023 with 748 participants. Results will be reported in 2024.

**Conclusions:**

This will be the first study providing key insights into respiratory health effects associated with using electronic cigarettes in people who vape with no established use of combustible cigarettes or other tobacco or nicotine products.

**International Registered Report Identifier (IRRID):**

DERR1-10.2196/54236

## Introduction

Electronic cigarettes (ECs) are battery-powered electronic devices that vaporize a water-soluble nicotine solution for inhalation. They do not create smoke or use combustion to operate. These consumer products have been rapidly gaining ground on combustible cigarettes (CCs) among smokers because of their potential for harm reduction from cigarette smoke and smoking cessation [1-3], their competitive price [4,5], and because of allowing people who smoke to continue having a “smoking experience without smoking” [6-8].

Considerable controversy persists surrounding the use of these products, particularly concerning potential misuse by nonsmoking youths and their potential negative impact on respiratory health [9-11]. Many studies examining nicotine vaping face challenges in data analysis due to participants having a history of CC smoking. This history might contribute to some of the adverse effects reported in prior studies, as highlighted in recent papers [12-14].

Under normal operational conditions (without overheating or dry burning coils), ECs present a significant reduction in exposure to harmful constituents compared to CCs [15-17]. No discernible negative health effects solely attributed to EC use (commonly known as “vaping”) have been conclusively established [18-20]. Analytical chemistry and toxicology studies of vaporized chemicals suggest no imminent health risks, although concerns persist about potential long-term respiratory implications [21-23]. Hence, further investigation into the prolonged health impact of persistent vaping is warranted.

The respiratory system is the most likely site for any potentially harmful effects of constituents in EC aerosol emissions. Only a few clinical studies have investigated the impact of regular vaping. No deterioration in lung function, airway responses, and respiratory symptoms were observed in a 1-year prospective randomized controlled trial of “healthy” people who smoked and were invited to quit or reduce their cigarette consumption by switching to ECs [24,25]. Specifically, FEF25-75% (a sensitive measure of obstruction in the more peripheral airways) [24], nitric oxide (a noninvasive biomarker of airway inflammation in airway disease as well as in studies of environmental and occupational exposure) [25], and carbon monoxide (an exposure unique to smoking, among tobacco product uses, causing airway inflammation and cardiovascular disease) in the exhaled breath returned to normal limits [25]. Similar results were observed for those who continued to use ECs versus those who quit using them. In addition, restoration of lung defense has been shown in smokers who had switched to exclusive use of ECs; they exhibited mucociliary clearance efficiency similar to that of a never-smoker and a former smoker [26]. Overall, these preliminary studies do not appear to suggest negative respiratory health outcomes in people who smoke and have switched to ECs.

Researching individuals who switch from CC smoking to ECs and then quit presents challenges in understanding their health outcomes. Studying the health of former smokers is complicated due to unknown health effects caused by previous smoking. Precise information about their smoking history—duration, quantity, and puffing behavior—alongside a large sample size is necessary to accurately control for these effects. Recent work by Sargent et al [13] underscores the importance of appropriately accounting for smoking history. They used data from the PATH (Population Assessment of Tobacco and Health) study and, by adjusting for the cumulative amount of CCs smoked (pack-years), demonstrated how using more refined analytical approaches revealed a previously significant association as nonsignificant. This highlights the substantial residual confounding present when using basic binary measures instead of more comprehensive assessments.

Therefore, only studies of people who vape but have never smoked CCs or have only a limited smoking history (ie, those who have smoked fewer than 100 CCs in their lifetime) can enable the detection of harms attributable to EC use. Without studies of people who use ECs with no established smoking history, it will be impossible to distinguish the harms of vaping from neither vaping nor smoking. Concluding that vaping poses less risk than smoking is easy [11,15-20,27-29]. Quantifying the absolute health risks of vaping independent of smoking requires cleaner data.

In a small study of daily EC users who had never smoked, no noticeable changes in blood pressure, heart rate, lung function, respiratory symptoms, exhaled breath nitric oxide, exhaled carbon monoxide, and high-resolution computed tomography of the lungs from baseline were observed over an average 3.5-year observation period [30]. Daily exposure to EC aerosol emissions caused no significant changes in any of the health outcomes investigated, including measures of lung function and lung inflammation. Moreover, no significant structural abnormalities were identified in the high-resolution computed tomography of the lungs, and no respiratory symptoms were consistently reported. Some of the strengths of this study included prospective rather than retrospective data collection from study participants; the detailed vaping history and precise characterization of the study participants; as well as the use of a panel of different clinical, functional, and inflammatory measures during the study.

Large prospective studies of well-characterized EC users with and without a history of CC smoking are warranted to establish the long-term effects of regular vaping on respiratory health. We will conduct a global cross-sectional survey of individuals from 6 world regions. Respiratory symptoms reported by a cohort of individuals who vape with no established history of CC smoking or other tobacco or nicotine product use will be compared against those reported by a cohort of matched controls with no established history of vaping, smoking, or use of any other tobacco products.

The primary aim of this study is to test the hypothesis that chronic exposure to EC aerosols does not cause an increase in respiratory symptoms among people who vape with no established cigarette smoking or other tobacco and nicotine product use history. The secondary aims are to determine the feasibility of assembling a large cohort of individuals who vape with no other established tobacco or nicotine product use history to evaluate such effects for future studies and to characterize patterns of vaping product use behavior among this unique cohort.

## Methods

An overview of the study is illustrated in Figure 1.

**Figure 1 figure1:**
[figure not shown]
Study design. The infographic illustrates the different stages of the study.

### Study Design

This will be a multicountry, cross-sectional, internet-based survey study. Individuals expressing an interest in participating in the study will be directed toward a website [31] with further information and will be screened using a brief questionnaire to assess their eligibility (Multimedia Appendix 1). All screening information gathered for contacts who are not potential recruits (ie, screen failures) will be discarded. Before conducting the survey, potential participants will be rescreened via telephone or email to confirm eligibility, to make sure they have an adequate understanding of the study, and to determine what language is required for the survey. Participants in the cohort will then be subjected to a web-based or mobile-based survey [32] using standard secure web-based survey tools, with central data collection. After completing the survey, participants will receive an email explaining how to redeem an Amazon or Take-A-Lot gift card code for an equivalent value of US $30, as appreciation for participating in the study.

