### Population

This study plans to recruit approximately 750 individuals globally, who satisfy the criteria for inclusion in either a cohort of “people who vape and who are nonusers of other tobacco or nicotine products” (“vapers cohort”; target N=500) or a cohort of “nonvapers who are also nonusers of other tobacco or nicotine products (“controls cohort”; target N=250), as defined in the following sections.

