### Statistical Analyses and Reporting

The primary objective of the study is to retrospectively estimate the effect of current, regular use of vaping products on respiratory symptom experience in the past 30 days, measured in this study by the mean score (0 to 5) on the 5-item RSES [35]. Details of sample size calculation and power analysis to detect differences in respiratory symptoms (ie, the RSES scores) between the “vapers cohort” and the “controls cohort” are included in Multimedia Appendix 1. In brief, with 75 participants per group, a study should be adequately powered to detect a difference of 0.57, the proposed minimal important difference, with a power of 98%. However, to detect a more conservative difference of 0.40, a study with 75 individuals per group would still have a power of 89%. The target study population will consist of approximately 500 exposed individuals and 250 matched controls–approximately 83 people who vape per each of the 6 world regions. If the initial recruitment falls short of the goal, or in the case of substantial early loss to follow-up, rolling enrollment will be considered to make up the deficit.

Data analysis of the RSES scores will be both descriptive and inferential in nature. The RSES scores and the demographic characteristics of the vapers cohort and the controls cohort will be descriptively summarized. We will test the null hypothesis that the RSES scores will not significantly differ between the vapers cohort and the controls cohort when adjusted for demographic differences. This hypothesis will be tested through a one-way between-subjects Analysis of Covariance in which the mean RSES score will be entered as the dependent variable, “Cohort” will be entered as the between-subjects independent variable, and 4 demographic variables—age, sex, education, and employment status—will be entered as covariates. Inferential and descriptive statistics will be reported for the Cohort variable adjusted for the effects of the covariates. *P* values <.05 will be considered statistically significant.

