The secondary objective of this study is to characterize the use of different vaping products by the vapers cohort. Data analysis of this objective will be purely descriptive in nature. Descriptive summary statistics will be reported for all questionnaire measures of vapers’ use of vaping products within each of the 3 product categories—disposable vapes, rechargeable prefilled pod vapes, and rechargeable refillable vapes. Data on the following variables will be descriptively summarized for the subsets of participants within the vapers cohort who are current users of each product category, as follows: number of current users, age of first use, age of first regular use, number of products used in a lifetime, number of product use days in the past 30 days, time of regular product use, the nicotine concentration of products used typically, type of e-liquid flavors used in the past 30 days, number of e-liquid flavors used regularly in the past 30 days, and number of products used in the past 30 days.

Descriptive summary statistics for continuous variables will include the number of participants in the population of interest (N), the number of participants in the population of interest with nonmissing data on the variable or measure (n), as well as appropriate measures of central tendency (eg, mean and median) and dispersion (eg, SD, SE, range, and IQR) for the observed data. Descriptive statistics reported for categorical variables or measures will include the total number of participants in each subject group who provided nonmissing responses, the proportion of each subject group who selected each categorical response option, and when appropriate, 95% CIs around the proportion of participants who selected each categorical response option.

Additional data analyses may be conducted where data on variables or measures are filtered or stratified by other independent variables of interest. If undertaken, the reporting of descriptive summary statistics for each variable or measure filtered and stratified by additional independent variables of interest will closely resemble the reporting of the planned analyses described above. All data analyses will be conducted using the IBM SPSS (version 27 or higher; IBM Corp) statistical software. Data tables not presented in primary reports or in the manuscript will be presented in supplementary files.

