## Results

Participant recruitment started in April 2023, and enrollment was completed by November 2023 with 748 participants. Results will be reported in 2024.

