Although this study promises important insights into respiratory symptoms and vaping behaviors among a culturally diverse group of adults who exclusively vape, it should be considered within the context of several limitations. First, its cross-sectional design limits the ability to draw conclusions about the causal relationship between vaping and respiratory symptoms. Longitudinal studies will be crucial to discern the prospective effects of vaping behavior on respiratory health. Second, the study’s reliance on nonprobability sampling methods may introduce a self-selection bias, impacting the generalizability of the findings to the broader population of exclusive vapers. However, given the rarity of this population subgroup, these methods were deemed the most practical approach to gathering a sufficient sample. Third, relying on a single respiratory health assessment (ie, RSES) based on self-report might introduce biases and inaccuracies. Participants might hesitate to disclose certain information or be influenced by social desirability bias, potentially affecting the data quality. Lastly, variations in survey interpretation due to linguistic, cultural, or regulatory differences across countries could lead to diverse responses, impacting the consistency and accuracy of the data collected for the research question.

The results obtained from the VERITAS study may offer crucial insights into the impact of vaping on health outcomes, providing a foundation for implementing essential public health measures. These findings can be effectively used within public health sectors and policies to address health concerns related to vaping, establishing necessary preventive measures to safeguard vulnerable populations. Moreover, the study methodology stands as a valuable reference for forthcoming research. Building such unique cohorts could serve as a pivotal resource for future studies, enabling the thorough examination of safety concerns and the quantification of potential risks or harm associated with vaping.

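### Discarding all screen-failure information leaves the feasibility aim only partly answerable: recruitment against target can be shown, screening yield and reasons for ineligibility cannot

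*Protocol article*

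**What the plan says.** The protocol article (Introduction, aims paragraph) gives two secondary aims. One is to "determine the feasibility of assembling a large cohort of individuals who vape with no other established tobacco or nicotine product use history", with future studies in view. The other is to describe patterns of vaping product use.

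The Discussion gives the reason for nonprobability sampling: "However, given the rarity of this population subgroup, these methods were deemed the most practical approach to gathering a sufficient sample".

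Under Study Design, people who express interest answer a brief eligibility questionnaire. On those who do not qualify the rule is: "All screening information gathered for contacts who are not potential recruits (ie, screen failures) will be discarded". No exception is made for counts or for reasons for failure.

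The Statistical Analyses and Reporting section names one secondary objective: "The secondary objective of this study is to characterize the use of different vaping products by the vapers cohort". Neither that section nor Study End Points gives a feasibility measure.

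The article does set recruitment targets. Population says: "This study plans to recruit approximately 750 individuals globally", made up of 500 vapers and 250 controls. Statistical Analyses and Reporting adds "approximately 83 people who vape per each of the 6 world regions". The Results section reports: "Participant recruitment started in April 2023, and enrollment was completed by November 2023 with 748 participants".

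**The concern.** For a rare group, feasibility has two parts. The first is whether the cohort could be assembled at all, and how quickly. The second is how much effort it took: how many people had to be screened for each eligible one, which criterion ruled the others out, and how this varied by region and recruitment channel. A team planning a follow-on cohort needs the second part to set its budget and choose its channels.

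The discard rule bears directly on that second part. It is a data-handling instruction fixed in the protocol, so it differs from a detail left open for an analysis plan. A plan can define a measure later, but it cannot restore records that have been deleted. The Discussion also offers the study's methodology as a reference for later research, and that reference is weaker without the screening denominator.

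**Working it through.** The article gives no feasibility figure, so there is nothing to reproduce. The check is to ask which feasibility quantities survive the rule as written.

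**Inputs from the article**
- Target: about 750, of whom 500 vapers and 250 controls (Population).
- Regional target: about 83 vapers in each of 6 regions (Statistical Analyses and Reporting).
- Achieved: 748 enrolled, April to November 2023, with no split by cohort or region (Results).
- Number screened, screen-failure rate and feasibility criterion: not given.

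**What can still be reported**
- Enrolment against target: 748 / 750 = 0.997, or 99.7%.
- Recruitment rate: 748 / 8 months = 93.5 per month, or 748 / 7 months = 106.9 per month, depending on how the end months are counted.
- Regional fill: 6 × 83 = 498, consistent with the target of 500. The survey records country of residence and assigns the cohort (Web-Based Survey Questionnaires), so fill by region and cohort can be tabulated from enrolled participants.
- Some later exclusions: the same section has people excluded on their survey-platform answers, after registration. The discard sentence belongs to the earlier screener and does not clearly reach these, so their counts may survive. They do not replace the denominator at first screening.

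**What cannot be reported if the rule is followed literally**

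The feasibility aim concerns people who vape, so the numerator should be the vapers and not all 748 participants. The achieved number of vapers is not given, so the target of 500 stands in for it. With number screened = 500 / yield, and the yields being assumptions:

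| Assumed yield | Screened for 500 vapers | Screened for 83 vapers in one region |
|---|---|---|
| 50% | 500 / 0.50 = 1,000 | 83 / 0.50 = 166 |
| 10% | 500 / 0.10 = 5,000 | 83 / 0.10 = 830 |
| 2% | 500 / 0.02 = 25,000 | 83 / 0.02 = 4,150 |

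All three rows end in the same enrolled cohort. The screening workload differs 25-fold between the first and the last (25,000 / 1,000), and the article contains nothing that tells them apart. Reasons for ineligibility, and yield by region or channel, are lost in the same way.

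**The case against.** The strongest reply is that the most direct test of feasibility is whether the cohort was assembled, where and in what time, and that this needs no screen-failure data. That stands. A reader might infer from the discard rule that the feasibility aim cannot be answered at all, or that the final enrolled count is all that remains. The article does not support either reading: it fixes targets overall, by cohort and by region, reports enrolment and dates, and collects what is needed for regional and cohort fill.

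Second, the rule may mean only individual answers from people who never entered the study, which would be ordinary data minimisation. Nothing expressly forbids an anonymous tally. This is fair, and the article does not settle it. But the sentence covers all screening information and provides for no tally, so it needs clarifying even on the kinder reading.

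Third, the absence of a feasibility measure from the analysis section might be read as a fault in itself. It is not counted as one here. This is a condensed article, and how a descriptive aim is summarised may properly sit in a fuller document.

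Fourth, a reader might expect screening counts to reveal selection bias. They would help little. Screen failures are ineligible people, and their number says little about how enrolled participants differ from eligible people who never came forward. Under Recruitment, vape shop owners ask clients about smoking and vaping history before referring them, so some filtering precedes the screener. The Discussion already discloses self-selection.

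Finally, enrolment is over, so a new prospective log is no longer possible. That limits the remedy but does not remove the point.

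**Conclusion.** The point holds in a limited form. Followed as written, the discard rule leaves the feasibility aim partly answerable. Recruitment against target (748 of about 750), time to recruit, and cohort and regional fill can be shown. Screening yield and reasons for ineligibility cannot, for a subgroup whose rarity the authors themselves cite.

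The size of the gap can only be illustrated: 1,000 to 25,000 people screened for 500 vapers, at assumed yields of 50% down to 2%. This rests on reading the rule as covering counts as well as individual records, and on using the target of 500 because the achieved number of vapers is not stated. If anonymous tallies were kept after all, the point reduces to a clarification of wording.

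The primary comparison of respiratory symptom scores is untouched. This is a cheap improvement to a secondary aim and does not threaten the study's main result.

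**What to change.** Amend the Study Design sentence so that identifiable screening records are deleted while anonymous counts are kept: screened, ineligible by first failed criterion, declined, and failed verification. Break these down by region, recruitment channel and intended cohort, and report yield for the vapers cohort separately from controls.

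Because enrolment is complete, the practical step is to retain and report whatever tallies the ambassadors and the web platform still hold, including exclusions made on the survey platform. If none exist, say so and limit the feasibility conclusion to recruitment against target, time to recruit, and fill by cohort and region.

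The cost is a one-sentence change and a small tallying task, with no identifiable data kept. The report should also note that counts starting at the screener miss the filtering done earlier by vape shop owners, so eligible / screened would not estimate how rare the group is in the population.
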